#### Joint trainee-supervisor activity

Each trainee-supervisor dyad will be encouraged to include a case-based discussion of evidence-based antibiotic prescribing in their regular weekly one-on-one teaching meetings. The supervisor will be offered a set of three or four structured cases to include in the meeting. This activity will be optional as the content of trainee-supervisor weekly meetings is at the discretion of the supervisors and trainees rather than the RTP.

The rationale for supplementing the educational intervention with supervisor educational activities was that our previous research suggested that the prescribing patterns (role-modelling) of supervisors and the ‘apprenticeship’ model of the trainee-supervisor relationship are drivers of non-rational antibiotic prescribing [9, 28].

### Recruitment

All GP trainees at the five training providers complete ReCEnT data collection in each of their training terms. This is part of their training program and includes reflection on practice and future training directions via detailed feedback [29]. The majority of GP trainees consent to the data being used for research purposes. The intervention will be conducted as part of their training program.

### Sample size calculation

It is expected that the intervention group will consist of approximately 130 GP trainees sourced from two intervention training providers and the control group of approximately 160 GP trainees from the control training providers. Each of these GP trainees will provide data on an average of four URTI consultations before the intervention and four URTI consultations after the intervention [9]. This will provide the study with approximately 80 % power to find an absolute reduction of 10 % in antibiotic prescribing for URTIs in the intervention group compared with the control group. This sample size calculation takes into account an inflation factor of 1.9 derived from an intracluster correlation of 0.27 from a similar study [12] and an anticipated proportion of consultations for URTI of 8 % and expected pre-intervention rate of antibiotic prescribing of 22 % as shown in the ReCEnT study [9].

### Data collection and analysis

Change in antibiotic prescribing will be assessed via ReCEnT data pre- and post-intervention. The changes in GP trainees’ prescribing will be compared with the changes of GP trainees of the two regional training providers who are not receiving the intervention (control group).

The principal analysis will be logistic regression within a Generalised Estimating Equation framework to adjust for clustering of observations within GP trainees. The unit of analysis will be consultations involving a respiratory tract infection and the outcome factor will be antibiotics prescribed (dichotomous). Independent variables in the model will be treatment group (intervention/control), time (before/after) and an interaction term of treatment group by time. The p-value of the interaction term will be used to determine statistical significance.

The dependent variables in regression models will be consultations in which antibiotics are prescribed (for URTI and acute bronchitis/bronchiolitis separately as the primary outcomes, and for URTI plus acute bronchitis/bronchiolitis (combined), acute otitis media, acute sinusitis and sore throat as the secondary outcomes).

We will also consider trainee, patient, practice and consultation related factors in the regression analyses. GP trainee factors will be age, gender, training term, place of medical qualification (Australia/international), and full-time/part-time status. Patient factors will be age, gender, Indigenous (Aboriginal or Torres Strait Islander) status, Non-English-speaking background status, whether new patient to the practice, and whether a new patient to the GP trainee. Practice factors will be rurality/urbanicity, socioeconomic status of the practice location, and practice size (number of GPs). Practice postcode will be used to assign the Australian Standard Geographical Classification-Remoteness Area (ASGC-RA) classification (the degree of rurality) of the practice location [30] and to define the practice location’s Socioeconomic Index for Area (SEIFA) Relative Index of Disadvantage [31]. Consultation factors will include the number of diagnoses/problems dealt with during the consultation, if the problem was a new one, and if the GP trainee sought clinical assistance during the consultation (from their supervisor/trainer, from a specialist, or from electronic or hard-copy resources).

Primary analyses will be by intention to treat (data of all GP trainees in the intervention group will be analysed irrespective of whether they attended the intervention workshop). We will also analyse the per protocol data (of only those GP trainees who attend the workshop) and compare these with the intention to treat analysis.

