### Study design

We will use a non-randomised non-equivalent control group design. Data for the analyses will be collected during the six-monthly rounds of ReCEnT data collection. The ReCEnT study is an ongoing prospective multi-site cohort study of GP registrars/trainees' consultations in five of Australia’s 17 Australian GP regional training providers [20]. ReCEnT longitudinally documents the nature and association of consultation-based clinical and educational experiences of early-career GPs (GP trainees). GP trainees record details of 60 consecutive consultations at approximately the mid-point of three six-month (full-time equivalent) terms based in general practices. Details recorded include patient demographics, diagnoses/problems managed, medications prescribed, investigations ordered, and assistance sought during the consultation (including supervisor advice and use of guidelines).

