### Setting

The intervention will be delivered once to GP trainees in two Regional Training Providers (RTPs). GP trainees in three control training providers will receive usual educational activities. These are five of the 17 RTPs in the Australian general practice vocational training program. The demographics of the GP trainees in the intervention group are broadly comparable to those of the control training providers.

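### Whole training providers receive the intervention, but the principal analysis clusters on trainee only, so any provider-specific change between rounds makes the interaction p-value too small

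*Protocol article*

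**What the plan says.** Under Study design: "We will use a non-randomised non-equivalent control group design". Under Setting, allocation is by provider: "The intervention will be delivered once to GP trainees in two Regional Training Providers (RTPs"), and "GP trainees in three control training providers will receive usual educational activities". Supervisors in the two intervention providers also receive the modules and a workshop.

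Under Data collection and analysis, the cluster level is named: "The principal analysis will be logistic regression within a Generalised Estimating Equation framework to adjust for clustering of observations within GP trainees". The model terms follow: "Independent variables in the model will be treatment group (intervention/control), time (before/after) and an interaction term of treatment group by time". So does the decision rule: "The p-value of the interaction term will be used to determine statistical significance". Trainee, patient, practice and consultation factors will also be considered. Provider is neither a cluster level nor a listed covariate.

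The same section describes the comparison group as "the two regional training providers who are not receiving the intervention (control group"), which conflicts with the three control providers under Setting.

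The Sample size calculation uses one "inflation factor of 1.9 derived from an intracluster correlation of 0.27 from a similar study", with no provider component. The limitations in the Discussion do not mention the small number of allocated providers.

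**The concern.** Trainees in one provider share a teaching programme. In the intervention providers they also share a workshop that reflects on the group's own prescribing data. The article itself names supervisors' role-modelling as a driver of prescribing. A local respiratory season, other teaching or a turnover of supervisors could therefore move a whole provider between two rounds. In the planned model such a shift enters the group-by-time term, while its standard error is computed as if about 290 trainees (130 + 160) varied independently. Recruiting more trainees per provider does not reduce this component; only more providers or more rounds would.

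At stake is what a significant interaction can support, for both primary outcomes. The article foresees offering the intervention to other training providers, which calls for inference beyond the few studied.

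**Working it through.** **Inputs from the Sample size calculation.** About 130 intervention and 160 control trainees; four URTI consultations each before and after, so 4 × 130 = 520 and 4 × 160 = 640 per round; baseline prescribing 22%; intracluster correlation 0.27; inflation factor 1.9.

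**Assumptions.** Two-sided 5% test (the article states no level); two against three providers, as under Setting; a provider-by-round standard deviation s of 1, 2 or 3 percentage points, independent between rounds. The article gives no value for s.

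**The plan's own figures.**
- The inflation factor is a trainee-level quantity: 1 + (4 − 1) × 0.27 = 1.81, and 1.9 needs about 4.33 consultations per cluster (1 + 3.33 × 0.27 = 1.90). Nothing is left over for providers.
- The stated power of about 80% does not follow from the stated inputs alone. Comparing 22% with 12% after the intervention only, with factor 1.9, gives 90.8%. The difference-in-differences that is actually tested gives 60%, 74% and 88% for pre-post correlations of 0, 0.27 and 0.5, and reaches 80% at about 0.38. This is a side observation. None of these versions contains provider-level variation.

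**Trainee-level variance of the difference-in-differences (risk scale).**

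V = f × 2 × 0.22 × 0.78 × (1/640 + 1/520) = f × 0.001196

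- f = 1 − 0.27 = 0.73 (trainee effects fully stable from before to after): V = 0.000873, standard error 0.0296.
- f = 1.9 (the protocol's factor, no pre-post correlation): V = 0.002273, standard error 0.0477.

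**Provider component left out.**

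E = 2 × s² × (1/2 + 1/3) = 1.667 s²

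This is 0.000167, 0.000667 and 0.0015 for s = 1, 2 and 3 points. The ratio of true to reported standard error is R = √(1 + E/V), and the true type I error is 2 × [1 − Φ(1.96/R)].

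| s (points) | R, f = 0.73 | Type I error | R, f = 1.9 | Type I error |
|---|---|---|---|---|
| 0 | 1.00 | 5.0% | 1.00 | 5.0% |
| 1 | 1.09 | 7.2% | 1.04 | 5.9% |
| 2 | 1.33 | 14.0% | 1.14 | 8.5% |
| 3 | 1.65 | 23.4% | 1.29 | 12.8% |

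At s = 2 points the reported standard error is too small by 1 − 1/1.137 = 12% (f = 1.9) to 1 − 1/1.328 = 25% (f = 0.73).

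**Simulation on the logistic scale.** Two separate simulations of 4,000 runs per setting used a trainee-clustered sandwich variance for the logit interaction.
- With s = 0, 1, 2 and 3 points, the first rejected in 5.0%, 7.4%, 11.2% and 19.3% of runs.
- With a between-provider standard deviation of the change of 0, 0.1, 0.2, 0.3 and 0.4 on the logit scale, the second rejected in 4.9%, 6.3%, 11.5%, 19.1% and 26.7%. A t-test on the five provider changes held 4.0-4.9% throughout.

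**If there are two control providers.** E becomes 2 × s² × (1/2 + 1/2) = 2s². With the same trainee numbers, s = 2 points gives a type I error of 9.2% (f = 1.9) to 15.7% (f = 0.73).

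**Price of a provider-level test.** The critical t is 3.18 on 3 df (two against three) or 4.30 on 2 df (two against two), against 1.96. With two against three providers and no provider variation, power for the 10-point effect is 31% (f = 1.9) to 63% (f = 0.73).

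**The case against.** The strongest objection is that the harm is conditional. A reader might infer that the planned p-value is certainly too optimistic, or that the type I error must exceed 5%. The documents do not support that. Stable provider differences largely cancel in the interaction, shocks common to all providers go into the time term, and with no provider-specific change the test is valid (4.9% and 5.0% in the simulations). The 1-3 point range has no source in the article. This stands, and it limits the finding to a mechanism with an assumed range of sizes.

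Other strong readings also fail:
- The ratio of 1.33 at s = 2 points might be read as an understatement of 33%. The true standard error is 33% larger than the reported one, so the reported one is 25% too small, and only under the most stable trainee effects.
- With two of five providers treated there are ten possible allocations, which might suggest that no exact p-value below 0.10 is attainable. The study is openly non-randomised, so those allocations are not a randomisation distribution.
- The interaction p-value might be called the sole criterion of success. The article says only that it determines statistical significance, and it specifies no confidence interval; the effect on an interval is implied.

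It is also fair to say that some provider-wide events, such as a regional campaign, are confounding, which no standard error corrects, and that wording cannot create more providers.

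The objection does not remove the point. The cluster level is stated explicitly, so this is not a detail left to an analysis plan, and the stated choice amounts to assuming zero provider-by-round variation.

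**Conclusion.** The concern holds in conditional form. Allocation is by provider, the stated analysis clusters on trainee only, and its standard error is right only if providers do not change differently between rounds. For assumed provider-by-round standard deviations of 1, 2 and 3 points, the true type I error is about 6-7%, 8-14% and 13-23%, where each range reflects the trainee-level standard error. These figures rest on two against three providers, a two-sided 5% level, 22% baseline prescribing and the planned numbers of trainees and consultations. The actual size cannot be known from the article. Against a 10-point target, a drift of 2 points is enough to change how a significant result should be read.

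**What to change.** 1. Keep the trainee-level GEE for the point estimate.
2. Report the pre-post change for each provider separately.
3. Prespecify a provider-level sensitivity analysis: a t-test on the provider changes, with 3 df for two against three providers or 2 df for two against two.
4. Where earlier ReCEnT rounds allow, estimate provider-by-round variation on the scale of the model (log-odds) and show it beside that test. The article mentions trainee data since 2010 but not how many rounds each provider has, so this estimate may be imprecise and should not be treated as known.
5. Do not simply move the GEE cluster to provider, because a sandwich variance from five clusters is unreliable. A provider fixed effect alone does not help either, since it leaves provider-by-round variation untouched.
6. State in the analysis and limitations sections that the trainee-clustered p-value and the stated power ignore provider-level variation and apply to these providers only.
7. Reconcile the number of control providers between Setting and Data collection and analysis.

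The cost is wording and some programming, with no new data collection. The downside is a wider interval, a less favourable power statement and a sensitivity test of low power.

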#### Workshops

The workshop component consists of a 1.5 h interactive workshop, scheduled as part of the standard training program for GP trainees and delivered at the premises of their RTP. We will use data on GP trainees' prescribing collected in the ReCEnT project to contextualise and reinforce the practical relevance and importance of the educational message (the ReCEnT data will be that of the workshop attendee trainees and their more senior colleagues who have been collecting ReCEnT data since 2010) [20]. During the workshop sessions, GP trainees will be asked to reflect on their group’s prescribing data and by means of clinical cases work through the main principles of rational prescribing of antibiotics informed by the authorative Australian guideline on antibiotic use (eTG). During the workshop there will be room for practising the communication skills presented in the online modules.

There will be ‘content’ discussion in the workshops, which will expand upon and explore some of the issues covered in the online modules. This discussion will present URTIs and acute bronchitis as exemplars of respiratory tract infections for which antibiotics are rarely indicated. Discussion will focus on these clinical syndromes, but the tenets of rational prescribing will also be applied to other non-pneumonia respiratory tract infections for which antibiotics have very limited indications (sore throat, acute otitis media, acute sinusitis).

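### In-consultation assistance-seeking, a post-intervention variable the programme could plausibly change, is listed among the adjustment factors; a model that includes it may not estimate the total effect

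*Protocol article*

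**What the plan says.** All references are to the protocol article.

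- **Principal model (Data collection and analysis).** A logistic GEE model clustered on trainee: "Independent variables in the model will be treatment group (intervention/control), time (before/after) and an interaction term of treatment group by time". The test is fixed too: "The p-value of the interaction term will be used to determine statistical significance".
- **Further factors (same section).** "We will also consider trainee, patient, practice and consultation related factors in the regression analyses". Trainee, patient and practice factors follow, then three consultation factors: the number of problems, whether the problem was new, "and if the GP trainee sought clinical assistance during the consultation (from their supervisor/trainer, from a specialist, or from electronic or hard-copy resources". All are named in one list; none is marked as different in kind.
- **How the item is recorded (Study design).** Among the details logged for each consultation is "assistance sought during the consultation (including supervisor advice and use of guidelines".
- **What the intervention works through.** In the workshop, trainees "work through the main principles of rational prescribing of antibiotics informed by the" national antibiotic guideline. Supervisors are offered the same online modules and a workshop of their own. Under Joint trainee-supervisor activity, the supervisor component is justified by earlier research suggesting that supervisor role-modelling and the apprenticeship relationship "are drivers of non-rational antibiotic prescribing".
- **Estimand.** The primary analyses are by intention to treat, so the quantity sought is the effect of the programme as a whole.

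**The concern.** Patient age or practice rurality cannot be altered by a workshop. Whether a trainee opens the guideline or calls the supervisor during a consultation can be. For after-period records in the intervention group, this item is measured after exposure and alongside the outcome. If the programme changes how often trainees look things up or ask, part of its effect on prescribing may run through that behaviour, and a model that holds the behaviour fixed estimates the effect net of that route.

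There is a second problem. Seeking help probably also reflects how uncertain or difficult the case is, which is itself a cause of prescribing and is only partly captured by the other listed factors. Conditioning on a variable that depends on both the intervention and case difficulty can induce an association between the two.

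What is at stake is the adjusted estimate. The design is non-randomised with a non-equivalent control group, so covariate adjustment is the natural answer to confounding. A term that changes what the interaction means weakens that answer.

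**Working it through.** **Step 1. Is the variable post-intervention?** Study design says it is logged in each recorded consultation and covers supervisor advice and guideline use. The outcome is prescribing in that same consultation. In the after period, the variable therefore follows the intervention.

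**Step 2. Could the intervention change it?** The sections on the INTRO modules, the workshops and the joint activity describe teaching built on the guideline, training for supervisors and encouragement to discuss antibiotic cases. Two of the sources of assistance in the covariate, the supervisor and reference resources, are channels the programme uses. A change is plausible. No section states it as an aim.

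**Step 3. Which model is affected?** The three-term principal model does not contain the variable. Any model that adds the listed consultation factors does.

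**Step 4. How far could the interaction move?** The plan has no figure of its own on this point. The following is an illustration.

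Inputs from Sample size calculation: prescribing of 22% before the intervention and a 10-point absolute reduction, so 12% after.

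Assumed inputs: no change over time in the control group; assistance sought in 10% or 20% of URTI consultations without the intervention (s0) and 5 to 30 points more with it (s1); an odds ratio for prescribing with versus without assistance (OR_A) of 0.5, 0.7, 1.5 or 2.0; no unmeasured common cause of assistance and prescribing.

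Total effect: log(0.12/0.88) − log(0.22/0.78) = −0.727, so OR = 0.483.

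Let expit(x) = 1/(1 + e^−x) and g = log(OR_A). Solve for a, then for d:

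- (1 − s0)·expit(a) + s0·expit(a + g) = 0.22
- (1 − s1)·expit(a + d) + s1·expit(a + d + g) = 0.12

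The assistance-adjusted OR is e^d, and the share of the log OR removed is 1 − d/(−0.727).

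Worked case, s0 = 0.20, s1 = 0.40, OR_A = 0.5: a = −1.148, giving prescribing of 24.1% without and 13.7% with assistance (0.8 × 24.1% + 0.2 × 13.7% = 22.0%). Then d = −0.609, giving 14.7% and 7.9% (0.6 × 14.7% + 0.4 × 7.9% = 12.0%). Adjusted OR = 0.544; share removed = 1 − 0.609/0.727 = 16%.

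Same frequencies with OR_A = 2.0: a = −1.425, d = −0.889, adjusted OR = 0.411, and the log OR is overstated by 0.889/0.727 − 1 = 22%.

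Over the grid:

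| Assumption | Adjusted OR (total 0.483) | Effect on log OR |
|---|---|---|
| OR_A 0.5 to 0.7, assistance up 5 to 30 points | 0.49 to 0.58 | about 2% to 25% removed |
| OR_A 1.5 to 2.0, assistance up 5 to 30 points | 0.38 to 0.47 | overstated by about 3% to 33% |
| Assistance frequency unchanged | 0.48 | shift under 1.5% |

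The small shift in the last row is non-collapsibility of the odds ratio, not mediation. If the programme lowered assistance-seeking, the first two rows would swap direction. Bias from unmeasured case difficulty is outside this calculation and has no known sign.

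**The case against.** The strongest reply is that the plan's decision rule is safe. The principal analysis is defined by three terms, its interaction p-value decides significance, and the further factors are only to be considered. Entry rules and the ranking of adjusted models are details an article commonly leaves to a fuller document. This stands as far as the principal result goes. It does not dispose of the point, because the article itself names this variable for the regression analyses and does not separate it from background confounders.

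Three stronger readings are tempting, and the document supports none of them.

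- **That the plan commits to adjusting for assistance-seeking.** The wording is that factors will be considered, and the variable is not fixed into the principal model.
- **That the intervention is designed to change assistance-seeking.** Its stated target is prescribing, through guideline principles, communication skills and supervisor influence. The dyad activity is optional and sits in weekly teaching meetings, not in the recorded consultation. Trainees who have absorbed the message might ask more, less or equally often.
- **That adjustment removes a known part of the effect.** A reader might multiply an assumed 10- to 30-point rise in assistance-seeking by an assumed 10- to 12-point difference in prescribing and report 0.10 × 10 = 1.0 to 0.30 × 12 = 3.6 points lost from the 10-point target. Neither input is in the document, the product is on the absolute scale while the model is logistic, and it counts attenuation only. The working shows that exaggeration is equally possible.

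**Conclusion.** The point holds in a limited form. Assistance-seeking is a post-intervention variable in the after period, it lies on channels the programme uses, and the article lists it with factors the programme cannot alter. In an adjusted model that includes it, the group-by-time term need not equal the total intention-to-treat effect. The principal analysis as stated is not affected, nor is the sample size.

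Direction and size cannot be determined from the document. The illustrative range, from about a quarter of the log odds ratio removed to about a third overstated, rests wholly on assumed frequencies and odds ratios, and the shift is negligible if the programme leaves assistance-seeking alone. The correction is still worth making: omitting the term loses little if the variable is unaffected by the programme, and protects the adjusted estimate if it is affected.

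**What to change.** 1. State that the three-term model remains the principal analysis.
2. Leave assistance-seeking out of every adjusted model that estimates the intervention effect. Keep the trainee, patient and practice factors, and also the number of problems and new-problem status. These last two carry case-mix information, and there is no reason here to drop them.
3. If assistance-seeking is of interest, analyse it as a separate process outcome by group and time, or in a mediation analysis labelled exploratory.

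The cost is one term removed from the covariate list for the effect models and a sentence of text. The item is already collected, so no new data are needed and the sample size calculation does not change.
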